**Effectiveness of health education interventions in cervical cancer screening behavior among women in slum areas of Pokhara Metropolitan, Nepal: study protocol for a quasi-experimental study**

**Abstract**

**Introduction**
Cervical cancer is a major public health issue in Nepal, particularly among women in low-resource settings like urban slums. Despite national screening guidelines, uptake remains low due to limited awareness, access barriers, and sociocultural factors. Community-based health education may help improve screening behavior.

**Methods**
A quasi-experimental study will be conducted in two slum areas of Pokhara Metropolitan City. Women aged 30–60 will be randomly selected and assigned to an intervention group (receiving CHW-led education using flipcharts and brochures) or a control group (receiving poster-based information). Data will be collected at baseline, three weeks, and six weeks using structured questionnaires. Outcomes include changes in knowledge, screening uptake, and health beliefs.

**Discussion**
This study will evaluate the effectiveness of CHW-led education compared to standard community information in improving cervical cancer knowledge and screening behavior. Results may guide scalable, community-based interventions to reduce cervical cancer burden in similar settings.

**Trial registration:** The study trial was registered in the Australian New Zealand Clinical Trials Registry (ANZCTR). Trial registration number: ACTRN12625000497404

**Introduction**

Cervical cancer ranks as one of the most prevalent cancers among women worldwide.^[1]^ The majority of cervical cancer-related deaths occur in low- and middle-income countries. ^[1]^ The incidence and mortality rates of cervical cancer vary among the World Health Organization’s (WHO) regions.^[1–3]^ The disparities across regions are attributed to inequalities in access to resources for prevention, screening, and treatment of cervical cancer, as well as social and economic factors such as poverty and gender biases. ^[1,4]^ Cervical cancer predominantly affects younger women, with 20% of children losing their mothers to this disease. ^[5]^

In 2020, cervical cancer was the leading cancer diagnosed among Nepalese women, resulting in the highest number of cancer-related deaths.^[6]^ The age-standardized incidence rate stood at 16.4 cases per 100,000 women, with 2,244 new diagnoses and 1,493 fatalities. ^[6]^ According to the national cervical cancer screening and prevention guidelines, women aged 30-60 are advised to undergo visual inspection with acetic acid (VIA) screening every five years, which initially targeted screening at least 50% of women aged 30 to 60 years, which was later revised to 70% in 2020. ^[7]^ However, by 2019, only 8.2% of women aged between 30 and 49 had undergone cervical screening in Nepal.^[8]^ Several obstacles, including limited awareness, limited trained healthcare professionals, and feelings of embarrassment, hinder the utilization of cervical cancer screening.^[9,10]^ On the other hand, factors like the gender of healthcare providers, effective counseling, and the privacy of screening services are frequently cited as facilitators for screening. ^[8]^

Community Information Channel-led interventions using posters are provided by the health facilities to aware women of cervical cancer. ^[7]^ According to the 2^nd^ amendment of the National Female Community Health Volunteer (FCHV) Program Strategy in 2076 BS, FCHV must have at least passed the SLC. ^[11]^ The fragmented nature of health programs poses a challenge for Female Community Health Volunteers to coordinate activities and deliver the results.^[12]^ So, an assessment of an integrated community health worker (CHW) program model is needed to support the implementation of community-based health interventions for the prevention and control of cervical cancer effectively.

**Methods**

**Study design and setting**

The study will be conducted in two slum areas of Pokhara Metropolitan, Nepal, implementing a quasi-experimental (pre-test-post-test control group) study design involving two groups: intervention (community health worker-led using flipchart and brochure) and control (community information channel led using poster).

**Study participants and sampling procedure**

Women aged 30-60 years from two slum areas of Pokhara Metropolitan City will be recruited as study participants. In the first stage, two slum areas of the Pokhara Metropolitan City will be selected purposively to ensure maximum matching between both slum areas, to ensure participants from both the control and intervention groups share similar characteristics. To control the potential confounding effect of accessibility on screening uptake, slum areas with similar distances to health facilities with VIA services will be selected. In the second stage, one slum area will be conveniently selected as the intervention group, and the other one will be conveniently designated as the control group. In the third stage, the list of women aged 30-60 years in both the selected slum areas will be prepared with the help of the head of the slum areas, and the participants will be randomly enrolled in the study.

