**Study process (Flow diagram)**

>33 Slum areas in Pokhara Metropolitan

2 slum areas will be purposively selected

One slum area will be conveniently chosen for control group

One slum area will be conveniently chosen for intervention group

Eligible women of 30-60 years will be completely enrolled (n=155)

Eligible women of 30-60 years will be completely enrolled (n=155)

Baseline data collection

CIC-led Intervention

CHW-led Intervention

1st Follow up, data collection (3^rd^ week)

2^nd^ Follow up, data collection (6^th^ week)

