**Figure 1: Study process (flow diagram)**

**Sample size calculation**

The sample size was calculated using screening rate at baseline study=73% (p1), the expected change in proportion up to 87% (p2), ^[13]^ with other values conventionally, as Z_a/2_=1.96 (for 95% CL), Z_β_=0.84 (β=80%), and using the formula for sample size (n)=[(Z_a/2_+ Z_β_)^2^. (p1(1-p1)+p2 (1-p2))]/(p1-p2)^2, we obtained 124.08 for each group. With an attrition rate of 20%, the final sample size for each group will be 155.

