**Data Analysis**

Statistical Package for Social Sciences (SPSS v22) will be used to store and analyze quantitative data. A descriptive analysis will be performed, where medians and interquartile range (IQR) will be used to characterize continuous variables, while frequencies and percentages will be used to summarize categorical data. P-values will be calculated, and less than 0.05 will be deemed statistically significant in all two-sided analyses, where needed, using the Pearson's chi-squared test, Mann-Whitney test, Wilcoxon test, and Mc. Nemar test. Effect size (r) in the Mann-Whitney and Wilcoxon tests will be calculated using the formula r=|Z|/√n ^[14]^. The intervals for small effect, intermediate effect, and strong effect are 0.1 to 0.3, 0.3 to 0.5, and 0.5 and higher, respectively ^[15]^. No interim analysis will be performed because of the short time duration.

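### The study team chooses by convenience which of two matched slums gets the CHW programme, so the choice can be steered, and the abstract's wording on assignment misleads

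*Protocol*

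**What the plan says.** The Protocol, under Study participants and sampling procedure, sets out three stages.

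- **Choice of the pair.** Two slum areas are picked purposively to be as alike as possible. The only matching criterion named is access: "slum areas with similar distances to health facilities with VIA services will be selected".
- **Choice of the arm.** Then "one slum area will be conveniently selected as the intervention group, and the other one will be conveniently designated as the control group". The flow diagram repeats this ("One slum area will be conveniently chosen for intervention group", with a matching box for control). Neither place gives a reason or a rule.
- **Choice of the women.** Eligible women are listed with the help of the slum head, and "the participants will be randomly enrolled in the study". This is the only random step.

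The Methods paragraph of the abstract opens with "A quasi-experimental study will be conducted in two slum areas of Pokhara Metropolitan City". Its next sentence says "Women aged 30–60 will be randomly selected and assigned to an intervention group", or to control. The title and the Study design and setting section also call the study quasi-experimental.

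**The concern.** Matching is meant to make the two slums interchangeable. If it succeeds, little scientific reason is left to pick the arm by hand. If it fails on something unmeasured, the hand choice is where bias can enter. Cooperation of the slum head and how well organised the women are do not appear among the matching criteria. Both could make a slum convenient for door-to-door work, and both could affect knowledge gain and uptake. The tests listed under Data Analysis (chi-squared, Mann-Whitney, Wilcoxon, McNemar) adjust for no covariates. Comparing changes from baseline would remove a stable difference in level, but not a difference in how readily a slum gains.

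The abstract adds a reporting problem. A reader who sees only that paragraph may believe that women were allocated to arms by chance. In fact each woman's slum fixes her arm before she is sampled.

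**Working it through.** **1. The texts side by side.** In the body and the flow diagram, the unit placed in an arm is the slum and the method is convenience. Chance acts later, on women within a slum. In the abstract, selection and assignment of women share one adverb. Only the selection half agrees with the body.

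**2. The plan's own figure.** Inputs from Sample size calculation: p1 = 0.73, p2 = 0.87, "Z_a/2_=1.96 (for 95% CL") and 0.84 for power.

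n = (1.96 + 0.84)² × (0.73 × 0.27 + 0.87 × 0.13) / 0.14² = 7.84 × 0.3102 / 0.0196 = 124.08, and 124 / 0.8 = 155.

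Both stated figures reproduce. Neither depends on how the slums are put into arms.

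**3. Expected bias if the choice is fully steered (assumed inputs).** Let slum means vary with SD τ = √ICC in units of the total SD, and let the more favourable slum always become the CHW slum. For two unmatched slums the difference is N(0, 2τ²), so the expected bias is E|difference| = 2τ/√π = 1.128τ. If matching induces a correlation ρ between the two slum means, this is multiplied by √(1 − ρ).

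| Assumed ICC | τ | Unmatched | ρ = 0.5 (× 0.707) | ρ = 0.8 (× 0.447) |
|---|---|---|---|---|
| 0.02 | 0.141 | 0.16 SD | 0.11 SD | 0.07 SD |
| 0.05 | 0.224 | 0.25 SD | 0.18 SD | 0.11 SD |

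For scale, the individual-level standard error of a mean difference with 124 analysed per arm is about √(2/124) = 0.127 SD. A weaker tendency to steer gives proportionally less. These figures concern outcome levels. For a change score, stable differences between slums partly cancel.

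**4. What a toss changes (screening uptake, assumed slum difference d, no intervention effect).** Take 73% in the less favourable slum and 124 analysed per arm, with se = √{[0.73 × 0.27 + (0.73 + d)(0.27 − d)]/124}. The chance of a significant result favouring CHW is 1 − Φ(1.96 − d/se) if the favourable slum gets CHW, and Φ(−1.96 − d/se) if it does not. A fully steered choice uses the first. A toss averages the two. For d = 0.05, se = 0.0545 and d/se = 0.917, giving 14.8% when steered.

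| d | Mean bias, steered | Mean bias, toss | False positive favouring CHW, steered | Same, toss | Two-sided error, either way |
|---|---|---|---|---|---|
| 3 points | 3 points | 0 | 7.8% | 4.2% | 8.4% |
| 5 points | 5 points | 0 | 14.8% | 7.5% | 15.0% |
| 10 points | 10 points | 0 | 48.2% | 24.1% | 48.2% |

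The nominal rate in that one direction is 2.5%.

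**5. What a toss leaves.** With one slum per arm and unmatched slums, the nominal 5% two-sided test has type I error 2[1 − Φ(1.96/√(1 + 123 × ICC))]. For assumed ICCs of 0.005, 0.01, 0.02 and 0.05 this is about 12%, 19%, 29% and 46%, even after a toss.

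**The case against.** The other side has four good arguments.

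- **Disclosure.** A reader might infer that the abstract claims a randomised trial. It does not clearly do so. The adverb can attach to the selection alone, which fits the third sampling stage, and the sentence before it says quasi-experimental. What stands is that the sentence is easily misread.
- **Sign.** A reader might infer that the bias must favour CHW education. The protocol gives no ground for the choice, so this is conjecture. On a 36-score knowledge scale with change as the primary outcome, a better organised slum might start higher and have less room to gain. Steering is possible, but its direction is not established.
- **Size.** The values 0.16 and 0.25 SD treat the two slums as unmatched and look at levels, whereas the plan matches the slums and its primary outcome is a change. They are upper illustrations, and the ICCs have no source in the document.
- **Remedy.** A reader might infer that a coin toss removes the bias. It removes only the steering. The realised difference between the two slums stays fully confounded with the intervention, and the plan declares two-sided tests ("less than 0.05 will be deemed statistically significant in all two-sided analyses"), whose error rate does not change. Nor is the toss entirely free: both slums must be able to supply ten women who have passed the SLC for the CHW role.

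These arguments narrow the point without removing it. Calling the study quasi-experimental discloses non-random allocation, but gives no reason to hand-pick a step that could be left to chance.

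**Conclusion.** The point holds in limited form. The Protocol leaves the arm of each slum to the team's convenience, with no stated rule, and the abstract's sentence misdescribes where chance enters. The choice can therefore be steered by features that may also affect the outcomes. The bias under full steering is at most about 0.16 to 0.25 SD on average if the slums are unmatched, and about 0.07 to 0.18 SD across the matching correlations shown. It is smaller again if steering is partial or if change scores cancel stable differences. All of this rests on assumed ICCs, matching correlations and degree of steering. The uptake illustration uses the outcome that sized the study, not the primary outcome, which is knowledge. A chance draw would make the expected bias from this step zero. It would not turn the study into a randomised comparison of women, nor solve the problem of one slum per arm. This is a low-cost improvement and a wording correction; it gives no evidence that the result will in fact be biased.

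**What to change.** - **Study participants and sampling procedure, and flow diagram.** Fix the two matched slums first. Confirm that each can host either programme, including ten SLC-passed women for the CHW role. Then have someone outside the study team decide the CHW slum by a witnessed, recorded coin toss. If only one slum can host the CHW programme, state that reason in place of convenience.
- **Abstract, Methods.** Write that women are sampled at random within two slums, and that the slum, not the woman, is assigned to an arm. Keep the term quasi-experimental. The flow diagram describes complete enrolment of eligible women, so reconcile it with random sampling when making this edit.

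**Cost.** One toss and a few sentences; 155 per group and the planned tests are unaffected. The team gives up the freedom to place the programme where it is easiest to run. Requiring both slums to be able to host it is an extra condition on site selection, on top of matching.

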**Outcomes**

The primary outcome will be a change in knowledge of cervical cancer. Secondary outcomes include changes in cervical cancer screening uptake, perceived susceptibility, perceived severity, and behavioral intention related to cervical cancer from baseline to midterm and endline assessments.

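### The intervention slum is designated before women are listed, enrolled and interviewed at baseline, and no concealment of the arm is stated, so entry and the baseline knowledge score are open to bias

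*Protocol*

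**What the plan says.** The Protocol's section on study participants and sampling numbers its steps. Two slums are chosen purposively. Then: "In the second stage, one slum area will be conveniently selected as the intervention group"; the remaining slum becomes control in the same step. Only after that: "In the third stage, the list of women aged 30-60 years in both the selected slum areas will be prepared with the help" (the helper being the local head), after which "the participants will be randomly enrolled in the study".

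The flow diagram has the same order. It shows "One slum area will be conveniently chosen for intervention group", with a matching box for control, then "Eligible women of 30-60 years will be completely enrolled (n=155" in each arm, then baseline data collection, then the two interventions.

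Under Data collection, knowledge is measured by trained female enumerators in face-to-face interviews with a structured questionnaire (14 questions, 36 points). Under Outcomes: "The primary outcome will be a change in knowledge of cervical cancer". Ethical considerations places written consent ahead of the study but does not relate it to the designation of the slums. The Intervention section puts the posters up once baseline is complete and draws ten CHWs from participants in the intervention group, without dating their selection.

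**The concern.** If the arm is known when women are being listed, invited and interviewed, the two groups can differ for reasons unrelated to the education. An area head may list more or less thoroughly. Women may agree or refuse according to whether home visits or only posters are on offer. An enumerator may probe or score differently.

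The primary outcome is a change from baseline, so both the make-up of the groups and the baseline score feed into the comparison. The tests named under Data Analysis cannot correct for who entered. Adjustment for measured characteristics such as age or education would not reach unmeasured willingness to learn or take part.

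This is separate from how the slum is picked. A random choice at stage two, announced at once, would leave it in place. Recruitment order is also fixed in the protocol and is not normally left to a statistical analysis plan.

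**Working it through.** **1. Order of events.**

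| Step | Sampling section | Flow diagram |
|---|---|---|
| Two slums chosen | Stage 1 | First |
| Arm designated, by convenience | Stage 2 | Second |
| Women listed with the area head | Stage 3 | Not shown |
| Women enrolled | Stage 3 (random) | Third (complete, n=155) |
| Baseline | Not shown | Fourth |
| Intervention | Not shown | Fifth |

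The two places agree that designation precedes enrolment. Women are identified only at stage three, so their consent must also come after designation. That is an inference, because the ethics section does not say so.

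**2. What the stated safeguards cover.**

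- Matching of slums and similar distance to screening services act between areas, not on who enters within an area.
- Random enrolment limits hand-picking from the list. It does not make the list complete or equalise refusal.
- Complete enrolment removes selection from the list, but still depends on the list and on consent.
- A structured questionnaire narrows scoring discretion but does not mask the interviewer.
- Concealment of the arm and masking of area heads, enumerators or women are not mentioned.

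**3. How a bias reaches the primary outcome.** Let D be the true between-arm difference in mean change, b the between-arm difference in baseline interviewing error, and f the same at follow-up.

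Observed difference = D + f − b

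If f = b, the error cancels. If interviewers are influenced at baseline only, the whole of b enters. Separately, suppose a share s of one arm gains g points more or less than the women who would otherwise have entered. The arm difference then shifts by s × g. The sign of g is open: interested women may learn more, or may start higher on the 36-point score and have less room to gain. The document gives no value for b, f, s or g.

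**4. Sensitivity, on assumed values only.** The plan's sample size reproduces: (1.96 + 0.84)² × (0.73 × 0.27 + 0.87 × 0.13) / 0.14² = 7.84 × 0.3102 / 0.0196 = 124.08 per group, and 124.08 / 0.8 = 155.1, stated as 155. It supplies n here and has no other bearing on the point.

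No standard deviation (SD) of the score is given, so let B be an assumed between-arm bias in SDs of the change score, with no true effect, independent women and a two-sided z-test at 0.05:

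P(significant) = 1 − Φ(1.96 − B√(n/2)) + Φ(−1.96 − B√(n/2))

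| B (assumed) | n = 124 per arm | n = 155 per arm |
|---|---|---|
| 0 | 5% | 5% |
| 0.1 | 12% | 14% |
| 0.2 | 35% | 42% |
| 0.3 | 66% | 75% |

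This shows how sensitive a trial of this size is to a modest bias. It is not evidence that such a bias will occur, and the planned rank tests would give somewhat different figures.

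**The case against.** **Designation is not disclosure.** The Protocol nowhere says that area heads, enumerators or women are told the arm before baseline. Posters go up afterwards, and the flow diagram puts the CHW visits after baseline too. The consent form is not in the copy at hand, so it cannot be said to reveal the arm. This stands: the gap is that concealment is not provided for, not that disclosure is planned.

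**Sampling already protects entry.** Random or complete enrolment does limit hand-picking, and this also stands. What remains is the completeness of the list, refusal and the interview. The two enrolment descriptions contradict each other, so it is unclear which protection applies. The Abstract's "Women aged 30–60 will be randomly selected and assigned to an intervention group" might be read as individual random assignment, but the sampling section assigns whole slums by convenience.

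**Direction.** A reader might infer that motivated women will enter the intervention arm and exaggerate the effect, or that a lower baseline score in one arm passes in full into its change. The document supports neither. Selection could work either way, and an interviewing error that persists at follow-up cancels.

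**The present order has one merit.** It fixes the arm before scores are seen. Simply exchanging stages two and three while keeping a convenience choice would let baseline results steer which slum gets the intervention. This stands, and it shapes the fix.

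**The gain is limited.** With one purposively chosen slum per arm, differences between slums are already inseparable from the intervention. That is true, but it does not excuse a further, avoidable source of bias.

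**Conclusion.** The point holds as a weakness in the order of recruitment. The arm is set before listing, enrolment and baseline, no concealment is stated, and the stated enrolment methods leave three routes open: incomplete listing, differential refusal and arm-aware baseline interviewing. Each could bias the between-arm difference in change in knowledge.

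Neither the size nor the direction can be estimated from the document. The sensitivity figures rest on assumed biases of 0.1 to 0.3 SD, independent women and a z-test. A reader might go further and conclude that the groups will be selectively filled or the baseline mis-scored. The Protocol does not support that, because it never says who knows the arm or when.

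The change is worth making before enrolment starts. The Protocol is written prospectively, and no baseline step it describes requires the arm to be known.

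**What to change.** Amend the sampling section and the flow diagram together:

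1. In both slums, first complete listing, eligibility checks, sampling, written consent in wording that does not reveal the arm, and every baseline interview.
2. Then assign the intervention slum by a random draw made without reference to the baseline data. Alternatively, if it is designated earlier, keep the designation concealed from area heads, enumerators and women until the last baseline interview, and state who holds it.
3. Select and train the CHWs and display the posters only after that. Choosing CHWs in one slum beforehand could itself disclose the arm.
4. State whether enrolment is random or complete, so that the sampling section and flow diagram agree, and bring the Abstract into line with assignment by slum.
5. Report refusals by slum.

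Cost: rewording of the sampling section, flow diagram, Abstract and, where needed, the consent text, with no extra participants. CHW selection and training cannot begin until baseline is finished in both slums. This is expected to be a short delay, but the Protocol gives neither the duration of baseline nor a date for CHW selection, so its length cannot be stated.

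The change does not remove the confounding from one slum per arm, or arm awareness at the follow-up interviews.
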